### Health economics

A within-trial economic evaluation will estimate the incremental cost and cost-effectiveness of PIFU compared with standard care from an NHS perspective. The base case analysis will take a 24-month time horizon. Data on NHS resource use over the 12 months before randomisation and the two-year study period will be obtained from participant questionnaires and hospital medical records. A sensitivity analysis will take a societal perspective and will also include costs incurred by patients, their families and employers. This will use data from patient-reported questionnaires on the cost of travelling to outpatient visits and time off work due to inflammatory arthritis.

To maximise statistical power and minimise patient burden, the analysis will focus on the medications, procedures, investigations and admissions that are most likely to drive the NHS cost difference between PIFU and standard care. Costing analyses will include the following resources: all outpatient consultations; all interactions with primary care professionals; accident and emergency consultations; DMARD medications for inflammatory arthritis; rheumatology advice lines; and procedures, investigations and admissions related to inflammatory arthritis disease process or treatments. The procedures, investigations and admissions related to inflammatory arthritis and treatment were prespecified in discussions between health economists and clinicians. This includes: relevant imaging such as musculoskeletal ultrasound; joint replacement; injection of intra-articular medications; and admissions for infection. Data on medications other than DMARDs will not be collected as they are not expected to have a material impact on incremental costs.

EQ-5D-5L will be used to estimate Quality Adjusted Life Years (QALYs); if no validated UK tariff is available, we will use the cross-walk tariff [28]. Cost-effectiveness will be expressed as incremental cost per QALY. Bootstrapping will be used to quantify uncertainty around costs, QALYs and cost-effectiveness ratios as 95% confidence intervals and cost-effectiveness acceptability curves. Analyses will adjust for covariates including demographics, costs in the 12 months before randomisation and baseline EQ-5D-5L. The economic evaluation will follow the National Institute for Health and Care Excellence (NICE) reference case [29] and Consolidated Health Economic Evaluation Reporting Standards (CHEERS) checklist [30].

Subgroup analyses will be conducted to see how costs, QALYs and cost-effectiveness vary between patient groups with different baseline characteristics. Sensitivity analyses will assess whether the conclusions are sensitive to changes in the methods and assumptions. A secondary analysis will extrapolate beyond the two-year time horizon, assuming that 24-month utilities will remain constant beyond month 24. This will assume biennial costs beyond month 24 will equal the costs in the trial other than any DMARD medication changes initiated at or by the 24-month visit. A further secondary analysis will reweight trial participants to generalise trial results to reflect the distribution of baseline characteristics in the wider population using data from OpenSAFELY. A distributional cost-effectiveness analysis will be performed to examine how incremental costs and QALYs of PIFU vary between income quintiles and assess the distributional implications of the policy. A health economics analysis plan (HEAP) will be prepared before data collection is completed.

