There are currently no studies ongoing assessing the effectiveness and cost-effectiveness of PIFU in the UK. A Cochrane review in 2020, addressing research across all long-term conditions, included data on 3402 patients, of whom 909 had inflammatory arthritis [8]. These four PIFU studies in rheumatology all had indicators of bias [9–12]. Three studies were single-centre and one studied two centres. All studies included only patients with RA and only one was conducted in the UK [9] well before the widespread use of biologic drugs that have had paradigm shifting effects on patient outcomes. We performed a meta-analysis of these studies, which showed that studies are inconclusive with respect to indicating whether PIFU is beneficial or harmful. As expected, PIFU is associated with fewer visits, consistent with ~1 fewer visit per-patient per-year, but a higher number of helpline calls [13]. It is uncertain whether these outcomes are generalisable to other centres, with different clinical pathways and to other conditions. A multi-centre randomised controlled trial is needed to establish whether PIFU is superior to standard care for people with inflammatory arthritis, and which patients benefit the most.

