### Trial design {12}

The TaILOR study is a multi-centre, two arm, parallel group, superiority, randomised controlled clinical study, with an embedded qualitative study and within-trial cost-utility analysis.

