### Sample size {19}

Three hundred and fifty participants providing data on the MSK-HQ score measured at 24 months post randomisation (175 per group) will provide 90% power to detect a difference in means of minimally clinically important difference (MCID) of 4 points [18], assuming a standard deviation of 11.5 points, using a two group t-test with a 5% (2-sided) significance level. This has been inflated to 438 (219 per arm) to allow for 20% attrition and crossover.

The MCID, estimated using the standard error as no anchor-based estimates were available [18], and the standard deviation of 11.5 points is estimated using Healthcare Quality Improvement Partnership (HQIP) National Audit for Early Inflammatory Arthritis Audit data [19]. There are no similar studies on which to base the estimated attrition rate, 20% is chosen to be conservative and in line with the wider RCT literature.

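### The plan gives the cost-effectiveness ratio a 95% confidence interval without condition and names no net-benefit measure; the interval cannot be read if the QALY difference is small relative to its standard error

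*Protocol article*

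**What the plan says.** In the protocol article, Table 1 lists cost per QALY gained over 24 months as the measure for the cost-effectiveness objective. The Health economics section says "Cost-effectiveness will be expressed as incremental cost per QALY" and "The base case analysis will take a 24-month time horizon". On uncertainty it says "Bootstrapping will be used to quantify uncertainty around costs, QALYs and cost-effectiveness ratios as 95% confidence intervals and cost-effectiveness acceptability curves". No net-benefit measure and no willingness-to-pay threshold is named, and nothing is said about draws that cross a QALY difference of zero. A health economics analysis plan (HEAP), not shown, is to follow before data collection ends. It is to be submitted for publication before any comparative analysis.

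Two other places bear on the likely result. Background and rationale reports from a meta-analysis that "studies are inconclusive with respect to indicating whether PIFU is beneficial or harmful", and also that "PIFU is associated with fewer visits, consistent with ~1 fewer visit per-patient per-year". The eligibility criteria require stable disease with no planned escalation of therapy.

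**The concern.** The ratio is the cost difference dC divided by the QALY difference dQ, and it is discontinuous at dQ = 0. Its sign is also ambiguous. A negative ratio arises when PIFU is cheaper and better, and also when it is dearer and worse. A positive ratio arises when PIFU is dearer and better, and also when it is cheaper and worse. If the draws lie on both sides of dQ = 0, ranking the ratios and cutting off the tails places opposite conclusions side by side. The two limits then do not bound a set of results with one meaning.

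Cost per QALY is the named cost-effectiveness measure. In that situation the plan would attach to it an interval that readers cannot use, with no interval estimate of the economic gain or loss to put in its place.

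**Working it through.** **The plan's own figure.** The documents state no QALY or cost variance, so the only figure to reproduce is the sample size.
- Normal approximation: n per arm = 2 × (1.960 + 1.282)² × 11.5² / 4² ≈ 174.
- t-test power at 175 per arm: 90.05%.
- Inflation: 350 / 0.8 = 437.5, so 438.

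The stated numbers reproduce. The powered effect is 4 / 11.5 = 0.348 SD on the MSK-HQ.

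**How precise dQ might be.** Assume a 24-month QALY SD of 0.2, 0.3 or 0.4 (not in the documents) with 175 per arm. Then SE(dQ) = SD × √(2/175). The share of draws below zero is Φ(−dQ/SE), taking the estimate equal to the true value. A bounded (Fieller) interval for the ratio exists only if dQ itself differs from zero at the 5% level. Its probability is Φ(dQ/SE − 1.96) + Φ(−dQ/SE − 1.96).

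| Assumed SD | SE(dQ) | dQ = 0: below zero / bounded | dQ = 0.02: below zero / bounded | dQ = 0.348 SD: below zero / bounded |
|---|---|---|---|---|
| 0.2 | 0.021 | 50% / 5% | 17.5% / 15% | 0.1% / 90% (dQ 0.070) |
| 0.3 | 0.032 | 50% / 5% | 27% / 10% | 0.1% / 90% (dQ 0.104) |
| 0.4 | 0.043 | 50% / 5% | 32% / 8% | 0.1% / 90% (dQ 0.139) |

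**What the ratio limits look like.** Assume dC = −£200 with SE £300 and SE(dQ) = 0.03, costs and QALYs uncorrelated, normal draws, and the 2.5th and 97.5th percentiles of dC/dQ. The limits for dQ = 0 and 0.02 move by a few thousand pounds between simulation runs. Net monetary benefit (NMB) is taken at an assumed £20,000 per QALY: NMB = 20,000 × dQ − dC, with SE = √((20,000 × 0.03)² + 300²) = √450,000 ≈ £671 and half-width 1.96 × 671 ≈ £1,315.

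| dQ | Draws below zero | Ratio limits | NMB and 95% interval |
|---|---|---|---|
| 0 | 50% | −£154,000 to +£155,000 | £200 (−£1,115 to +£1,515) |
| 0.02 | 25% | −£126,000 to +£120,000 | £600 (−£715 to +£1,915) |
| 0.104 | almost none | −£9,900 to +£4,200 | £2,280 (+£965 to +£3,595) |

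At dQ = 0 the draws split 37% cheaper and better, 37% cheaper and worse, 13% dearer and better, 13% dearer and worse. At dQ = 0.02 the split, in the same order, is about 56%, 19%, 19% and 6%. With SE(dQ) anywhere from 0.021 to 0.043 and dQ from 0 to 0.02, the limits stay between roughly £95,000 and £220,000 either side of zero. The NMB interval has the same width in every row.

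**Repeated trials.** A simulation of the percentile interval assumed QALY SD 0.3, cost SD £2,500, dC = −£200, correlation −0.1 and 175 per arm.

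| True dQ | Coverage of the true ratio | Trials with more than 2.5% of draws on each side of zero |
|---|---|---|
| 0.005 | 88% | 95% |
| 0.02 | 98% | 90% |
| 0.06 | 98% | 53% |
| 0.104 | 96% | 9% |

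Coverage falls clearly short only very close to zero. Elsewhere the numerical coverage is adequate, and the defect is that the interval mixes quadrants and has no usable reading.

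**The case against.** A reader might infer that the documents expect a QALY difference near zero, so that the interval would fail in the most likely scenario. They do not support this. No section gives an expected QALY difference, and inconclusive evidence from earlier studies is not a forecast of no effect. The design points the other way: "The TaILOR study is a multi-centre, two arm, parallel group, superiority, randomised controlled clinical study", powered for a "minimally clinically important difference (MCID) of 4 points". If QALYs moved by the same standardised amount, the ratio interval would usually be satisfactory. A small dQ is therefore a plausible case and no more.

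A second stronger reading is that decision uncertainty is left without any valid summary. That also fails. The same sentence plans acceptability curves and separate intervals for costs and QALYs. Curves built from net benefit remain valid at dQ = 0. They give a probability at each threshold, however, and not an interval for how much is gained or lost.

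Third, the sentence does not name the percentile method, and it lists three quantities and two outputs without pairing them. It could mean intervals for costs and QALYs and curves for cost-effectiveness. This has some force, but the plain reading includes an interval for the ratio. When dQ is not clearly non-zero, no choice of bootstrap limits makes that ratio well behaved.

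Fourth, presentation detail belongs in the HEAP. That would answer a complaint about something missing. The point here is a method that the article states without condition. The HEAP may already qualify it, and it is the right place to do so.

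**Conclusion.** The point holds conditionally. The plan commits to a 95% interval for the cost-effectiveness ratio whatever the QALY result, and names no net-benefit measure. If dQ is small relative to its standard error (in the illustration, 0 to 0.02 against 0.021 to 0.043), between 17.5% and 50% of draws fall below zero QALYs and the ratio limits cannot be read as a confidence interval. If dQ is clearly away from zero, as at 0.104 with SE 0.03, the interval is acceptable.

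These sizes rest on assumed QALY and cost variances, an assumed cost difference of −£200 and an assumed threshold of £20,000, none of which the documents give. The direction of the argument does not depend on them; how often the problem would arise does. This is a free improvement, confined to the secondary economic analysis. It does not touch the primary MSK-HQ comparison or the sample size.

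**What to change.** State in the HEAP, and in the protocol at its next amendment:

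- Incremental net monetary benefit, with a 95% confidence interval at prespecified threshold(s), is the main measure of uncertainty for cost-effectiveness.
- It is shown with the cost-effectiveness plane and the acceptability curves already planned, the curves being built from net benefit.
- The ratio is reported as a point estimate. An interval is added only when the bootstrap draws do not materially straddle a zero QALY difference, with the cut-off fixed in advance in the HEAP.

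The cost is a few lines of text. The same bootstrap draws serve, no further data are needed, and the change can be made before any comparative analysis.

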### Interim analyses {28b}

The main outcomes will be analysed as stated in the analysis plan once the study follow-up has been completed. No formal interim analyses of treatment effect are planned for any of the study outcomes.

As no formal interim analyses are planned, no stopping rules have been incorporated into the study design. An independent DMC met early in the trial to agree its terms of reference. They will review the confidential accumulating data at regular intervals and can recommend pausing or stopping the study in the event of safety concerns.

An internal pilot with predefined stop–go criteria to assess feasibility of recruitment was reviewed after 3 months of recruitment. The internal pilot study mirrored the procedures and logistics undertaken in the main definitive study. Predefined stop–go criteria and outcome of this pilot phase are outlined in Table 4.

**Table 4 Tab4:** Internal pilot criteria and progression guidance

Progression guidance	Criteria	Outcome
Continue with study — no action required	**Recruitment** = 75% + of 3 month target (68 participants) **Number of centres opened** = 20 +	**Recruitment**: 76 participants **Number of centres opened**:25 **Action**: Continue with study, no action required
Continue with study — action required: 1. Review recruitment strategies and modify/monitor closely 2. Report to TSC	**Recruitment** = 50–75% of 3 month target (45–67 participants) **Number of centres opened** = 10–20	
Stop	**Recruitment** = <50% of 3 month target (45 participants) **Number of centres opened** = <10	

The TMG closely monitored the progression criteria, and together with the TSC and DMC performed a full review at the end of the internal pilot. At the time of the review, the study met the ‘green’ progression guidance to continue with the study with no action required. Therefore, the study progressed seamlessly into the main phase. Data from the internal pilot will contribute to the final analysis.

### Protocol and statistical analysis plan {5}

The SAP and HEAP will be submitted for publication in an open-access peer-reviewed journal in accordance with the Guidelines for the Content of Statistical Analysis Plans in Clinical Trials [31] prior to any comparative analyses.

## Oversight and monitoring

### Composition of the coordinating centre and trial steering committee {3d}

The study will be coordinated by OCTRU based at the University of Oxford. A TMG will be established for the study and operate in accordance with a study-specific TMG charter. The TMG will manage the study, including the clinical and practical aspects, and will meet approximately monthly to assess progress. Other specialities/individuals will be invited as required for specific items/issues.

### Trial steering committee

The TSC, which includes independent members, provides overall supervision of the study on behalf of the funder. The TSC will act in accordance with a TSC charter which will outline its roles and responsibilities. Full details including names will be included in the TSC charter. Meetings of the TSC will take place at least once a year during the recruitment period. An outline of the remit of the TSC is to:Monitor and supervise the progress of the study towards its interim and overall objectivesReview at regular intervals relevant information from other sourcesConsider the recommendations of the DMCInform the funding body on the progress of the study

The TSC will consider, and act, as appropriate, upon the recommendations of the DMC

### Composition of the data monitoring committee, its role and reporting structure {28a}

An independent DMC was established for this study. The DMC will adopt a DAMOCLES-based charter, which defines its terms of reference and operation in relation to the oversight of the study. The DMC will meet regularly throughout the study at time-points agreed by the Chair of the Committee and the CI. At a minimum this will be on an annual basis. The DMC will review the patient reported flare data generated and make recommendations as to whether the protocol should be amended to protect patient safety. Recommendations of the DMC will be discussed between the CI, TSC, and the Sponsor.

### Frequency and plans for auditing trial conduct {29}

All aspects of the study conduct may be subject to internal or external quality assurance (QA) audit to ensure compliance with the protocol, GCP requirements and other applicable regulations or standards. Such audits or inspections may occur at any time during or after the completion of the study. Investigators and their host.

### Protocol amendments {31}

All amendments will be generated and managed according to the CTUs SOPs to ensure compliance with applicable regulation and other requirements. Written confirmation of all applicable Research Ethics Committee (REC), Sponsor and local approvals must be in place prior to implementation by investigators as applicable for the amendment type. The only exceptions are for changes necessary to eliminate an immediate hazard to study participants in the case of an urgent safety measure to protect study participants from any immediate hazard to their health or safety.

It is the Investigator’s responsibility to update participants (or their authorised representatives, if applicable) whenever new information becomes available that might affect the participant’s willingness to continue in the study. The Investigator must ensure this is documented in the participant’s medical notes and the participant is re-consented if appropriate.

### Dissemination policy {8}

The Sponsor will retain ownership of all data arising from the study. Publication and dissemination of study results will be in accordance with OCTRU SOPs and irrespective of study findings. The study results will be published in an open-access journal, in accordance with the NIHR’s policy on open-access research as well as appropriate conferences. The study will be reported following the Consolidated Standards of Reporting Trials guideline (CONSORT) including any applicable extensions to this. The Template for Intervention Description and Replication (TIDieR) statement will be used for reporting the intervention.

All data will be presented such that no individual participants can be identified. Publications may include direct quotations from the qualitative interviews.

A summary of the study results for study participants will be written collaboratively with clinicians and patient representatives and distributed to study participants by the Central CTU Study Office, unless an individual has stated they do not wish to receive such a summary. The PIS will also include a link to the study website where participants will be advised that the results will be published. Findings will also be available via the CTU website and social media. Newsletters, social media, and relevant patient-facing charities will also be used to ensure the results of the study are communicated to the wider community once they are available.

A stakeholder engagement event is planned to discuss the results, interpretation and policy implications and both this study and the findings of the observational study with the research programme. Key stakeholders for such a meeting, with a focus on diversity in representation, would be patients, rheumatology teams, hospital managers and NHSE. The outcome of this meeting will form an additional research output from the project and we believe would be of great interest to patients, clinicians and policy makers internationally. We will also share our findings to support work in other speciality areas, primarily through our links with relevant NHS teams.

Authorship for future trial publications will be determined in accordance with the ICMJE criteria. NIHR Associate Principal Investigators will be recognised under group authorship, and professional medical writers will not be used.

## Discussion

Inflammatory arthritis comprises lifelong conditions, such as RA, AxSpA and PsA that require long-term treatment and regular monitoring of disease and treatment. The implementation of PIFU where patients request appointments as required may offer an opportunity to empower patients, supporting self-management and a sense of control over healthcare decisions. It could improve patients’ experience of care and enable clinicians to focus their attention on those whose clinical need is greatest. However, there are concerns from patients and clinicians that PIFU should not compromise patients’ short-term or long-term outcomes, nor result in increased health inequalities and that PIFU should be tailored to the individual patient and the service concerned. To date, there are small studies of PIFU in RA and none in other arthritis. The research within the TaILOR programme of work is required to provide further data on PIFU across different forms of inflammatory arthritis in the UK. This can help to configure services to optimise outcomes, reassure patients and clinicians of the effectiveness and safety of PIFU and ensure that suitable patients are selected for this pathway.

### Trial status

Protocol version 2.0 (20 January 2025) was approved on 22 January 2025. The study opened to recruitment on the 21 March 2025 and was initially expected to close by 31 December 2025. Protocol V3.0 (04 December 2025) was approved on 04 December 2025 to extend recruitment by 1 month (ending 31 January 2026).

## Data Availability

Upon completion of the study, anonymised research data may be shared with other organisations on request to the CI and in accordance with the data sharing policies of OCTRU, the Sponsor and funder(s).

